#### The Activate intervention

The Activate intervention is developed for patients at risk for CVD. The intervention is standardised in four nurse-led consultations to enhance physical activity—in the first week and after 2, 6 and 12 weeks—and will take place in the patient’s own general practice. Although the BCTs are systematically applied in the intervention, the content of the intervention will be individualised to the patient’s unique circumstances, needs and preferences by adapting the BCTs during the consultations (e.g., goal setting, action planning, feedback). The duration of the first consultation is 30 minutes, and the subsequent consultations last 20 minutes. During the first consultation, patients will receive a workbook containing information about the study, useful websites and apps, tips and tricks, activity logs and action plans.

In the first consultation, the nurses will discuss the patient’s CVD risk profile, the consequences of a sedentary versus an active lifestyle, and self-assessment of their activity level in order to raise awareness to improve the patient’s level of physical activity. Together, the patient and nurse formulate an overall outcome goal and an exercise goal, considering physical activity in minutes per day. In order to raise awareness of self-monitoring and how to self-monitor, the patient is asked to self-monitor physical activity during the next 2 weeks by using an accelerometer and a paper activity log, which provide feedback on the patient’s level of goal attainment. Additionally, the patient is asked to identify facilitators to goal attainment.

During the second consultation, the nurse rehearses the information about the consequences of an active lifestyle, reviews the goal attainment using the activity log kept by the patient, and discusses the identified facilitators. If applicable, the physical activity goal is re-formulated. A specific action plan to attain the level of physical activity formulated as their goal is set up. The patient is supported in finding ways to use facilitators for physical activity, is asked to self-monitor activities during the next weeks in order to attain the set physical activity goal, and is asked to identify possible barriers to goal attainment.

In the third consultation, the nurse will give feedback on the reached level of goal attainment during the past weeks, using the log kept by the patient. If applicable, the activity goal and specific action plan are adjusted. Furthermore, the nurse will discuss how to prevent relapse into an inactive lifestyle (old habits) by discussing the barriers leading to relapse as well as how to build new habits to maintain the active lifestyle. The patient is asked to self-monitor activity level during the next weeks in order to attain the set physical activity goal and to identify possible barriers to and facilitators of goal attainment.

In the last consultation, the nurse will give feedback on the reached level of goal attainment during the past 6 weeks, using the results of the patient’s self-monitoring and activity log and the identified facilitators. Furthermore, the nurse will rehearse how to prevent relapse into old habits and the formation of new activity habits.

The nurses will be provided with several resources, which they can use during their consultations. They will have a workbook for each patient in which charts (what to do when) and example sentences are given to help them deliver the BCTs effectively. In addition to the individual coaching sessions, nurses will be asked to watch the videos on how to apply the BCTs in the intervention to reinforce their skills and competencies in delivering the Activate intervention. The division of selected BCTs between the different components of the training is shown in Table 2.

### Feasibility and piloting

The training for nurses was pilot-tested in a small feasibility study. To evaluate whether the consultations were feasible in time and to ensure the intervention matched with the patient’s needs and could be incorporated into daily life, two primary care nurses completed the training, and one patient at risk for CVD completed the consultations. Their experiences, barriers, strengths, limitations and time investments were evaluated. The nurses indicated that the training adequately equipped them to deliver the intervention. They suggested minor adaptations, namely inclusion of patients across a broader age range (40–75 years), easier interpretation of level of adherence to the Dutch Norm for Healthy Exercise according to the SQUASH, and clear instructions on how to recruit and include patients. The time spent on the consultation was acceptable and in accordance with the protocol. The patient was satisfied with the intervention and suggested minor adaptations in the layout of the activity log.

### Care as usual

Patients in the control arm will receive care as usual, according to the national health care standards for patients at risk for CVD [16], during regular consultations with their nurse and will not receive additional consultations beyond standard of care to increase their physical activity level. Patients at risk for CVD have at least one consultation per year with their nurse; however, this frequency can be extended when considered necessary (e.g., in case of medication change). Patients with DM2 have at least four consultations with their nurse annually. In order to keep the nurses in the control arm motivated, the 1-day training will be offered to them at the end of the study.

### Data collection

To assess the characteristics of the nurses participating in the study, a short questionnaire will be sent to nurses. To assess whether patients are eligible for improving their level of physical activity, patients are asked to fill out a short self-assessment using the SQUASH prior to consenting to participate in the study. Nurses will interpret the completed SQUASH using clear guidelines to see if a patient fits the inclusion criteria regarding insufficient level of physical activity. After enrolment, patient data will be collected at baseline (T0), after 3 months (T1) and after 6 months (T2) by use of an accelerometer, questionnaires and chart review (see Fig. 2). At time point T0, the nurses will distribute the questionnaires and accelerometer after enrolment during their regular scheduled visit. At time points T1 and T2, the research team will distribute the questionnaires and accelerometers. To maximize retention of general practices, the research team will contact each general practice regularly, and nurses can easily contact the research team for remarks and questions. Nurses will receive a monthly newsletter to keep them updated on the number of recruited patients in the other attending general practices and to invite them to share their experiences with other nurses. To maximize retention of patients, the research team will contact patients by telephone or e-mail if no questionnaire and accelerometer are received within 3 weeks. If the research team is not able to contact the patients after several attempts, we will ask the attending nurse to contact the patient. Furthermore, patients are encouraged to contact the research team if they have remarks and questions.

#### Data management

Data collection as well as handling and storage of data and documents will be coordinated at the University Medical Center Utrecht. Entering of objective data collected from the accelerometers will automatically be uploaded from the accelerometer by two researchers on the research team. Entering of subjective collected data will be performed electronically by an independent data manager who is not aware of patient allocation.

### Outcome measures

#### Primary outcome

The primary outcome is physical activity objectively measured as the number of minutes of physical activity in the moderate to vigorous category. This will be assessed with a personal activity monitor (Pam AM300; Pam bv, Oosterbeek, The Netherlands) [46]. The Pam AM300 is a small, valid, and reliable triaxial accelerometer which can easily be worn on the hip. Additionally, patients will be asked to write down in a paper log the amount of minutes they have swum, cycled or done strength training, because the accelerometer cannot measure these activities accurately.

The number of minutes of physical activity in the moderate (3–6 metabolic equivalents [METs]) and vigorous (≥6 METs) categories at 6 month of follow-up will be considered as the primary outcome measure. Patients will be asked to wear the accelerometer during 7 consecutive days for 12 h daily at baseline (T0), at 3 months of follow-up (T1) and at 6 months of follow-up (T2). For a valid measurement, the accelerometer has to be worn for at least 4 weekdays and 1 weekend day for 8 h. After each data collection point, patients will be asked to send the accelerometer to the research team to upload the data from the accelerometer to a data file. The outcome is the average number of minutes of moderate to vigorous activity on all the valid days. With the Activate intervention, a mean difference in minutes of 20% of at least moderate level of physical activity from baseline is considered to be clinically relevant and reasonable to achieve within 3 months of intervention.

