5.	Review behavioural goal(s) (e.g., examine how the patient worked on the agreed goal, and consider re-setting, modifying or continuing with the agreed goal)		x	x	x
6.	Commitment (e.g., ask to affirm the agreed goal and action plan)		x	x	x
7.	Feedback on behaviour (e.g., give feedback using the personal activity log)	x	x	x	x
8.	Self-monitoring of behaviour (e.g., ask to wear the accelerometer and to fill in the personal activity log daily)	x	x	x	x
9.	Social support (unspecified) (e.g., encourage support from patient’s spouse or ‘buddy’)		x	x	x
10.	Social support (practical) (e.g., encourage practical help from patient’s spouse or ‘buddy’)		x	x	x
11.	Information about health consequences (e.g., inform about health benefits of physical activity)	x	x		
12.	Prompts/cues (e.g., advise to use the Post-Its and the pen with the study logo to remind of physical activity)		x	x	x
13.	Habit formation (e.g., prompt to rehearse and repeat the planned daily activities)			x	x
14.	Graded tasks (e.g., assist to increase the level of activity step by step by agreeing with achievable and challenging goals)		x	x	x
15.	Restructuring the physical environment (e.g., advice to repair the bike, buy good shoes or rain clothes)		x	x	x
16.	Restructuring the social environment (e.g., advise to go walking with a friend instead of drinking coffee)		x	x	x
17.	Focus on past success (e.g., encourage to think about occasions on which the patient succeeded in being physically active)	x	x	x	x

*Abbreviations*: *BCTTv1* Behaviour Change Technique Taxonomy v1, *BCT* Behaviour change technique

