#### Secondary outcomes

The following are secondary outcomes of this trial:Sedentary behaviour using the accelerometer to measure the number of minutes in the sedentary category (<1.8 METs)Self-efficacy for physical activity using the Exercise Self-efficacy Scale [47–49]Patient activation using the PAM-13 short form [50, 51]Health status using the EQ-5D questionnaire [52]

Potential effect modifiers to investigate which patient characteristics modify change in physical activity level include age, depression measured using the Hospital Anxiety and Depression Scale [53, 54], body mass index (BMI), level of education, social support using the Multidimensional Scale of Perceived Social Support [55], patient-provider relationship using the Communication Assessment Tool [56], and baseline number of minutes of moderate to vigorous level of physical activity using the accelerometer.

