### Statistical analysis

#### Effectiveness of the activate intervention

Data will be analysed primarily according to intention to treat and secondarily according to per-protocol principles. All patients with outcome data will be included in the intention-to-treat analysis, regardless of their adherence to the intervention. Patients in the intervention group will be included in the per-protocol analysis if they received a minimum of three consultations (75%), based on the registration forms obtained from the nurses. Patients from both groups were excluded from this analysis if they did not complete the T1 measurement. To examine the effect of the Activate intervention between the arms, a multilevel analysis will be performed (three levels: time, participant and general practice). The continuous outcome data will be quantified by mean, SD and 95% CI using linear mixed effects models. For the binominal outcome data, risk ratios and 95% CIs will be estimated using generalised estimating equations (GEEs) with a log-link function. In case of non-convergence of a model, ORs will be estimated using a logistic mixed effects model. All mixed effects models include a random intercept for changes over time and between practices. An interaction term will be added for time and study arm. Missing data will be handled according to the rules of the questionnaires of missing data. Missing outcome data will not be imputed, because multilevel analysis is a flexible method for dealing with missing outcome data [59]. Sensitivity analyses, such as an analysis of protocol deviations, definitions of outcomes, and outliers, will be performed to assess the robustness of the findings.

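### Sedentary behaviour is defined as raw minutes although a valid day may be 8 h or 12 h and more, so it mixes sitting with device wear; the same risk to the primary outcome is smaller and conditional

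*Protocol article*

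**What the plan says.** Under Primary outcome, the wear instruction is "Patients will be asked to wear the accelerometer during 7 consecutive days for 12 h daily", at baseline (T0), 3 months (T1) and 6 months (T2). The validity rule is lower: "For a valid measurement, the accelerometer has to be worn for at least 4 weekdays and 1 weekend day for 8 h". No maximum is set. The primary outcome is a plain mean of minutes: "The outcome is the average number of minutes of moderate to vigorous activity on all the valid days".

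Under Secondary outcomes, sedentary behaviour is also a count, "using the accelerometer to measure the number of minutes in the sedentary category", with the category set at below 1.8 METs.

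The section on effectiveness of the intervention gives the three levels of the mixed model, a random intercept and a time-by-arm interaction. It names no wear-time term and no standardisation. It adds only a general provision: "Sensitivity analyses, such as an analysis of protocol deviations, definitions of outcomes, and outliers, will be performed". The Discussion treats other limits of accelerometry but not wear time.

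In Table 1, item 8, accelerometer use is also part of the treatment: "Self-monitoring of behaviour (e.g., ask to wear the accelerometer and to fill in the personal activity log daily". The care-as-usual section describes nothing similar for controls.

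**The concern.** Sedentary minutes can be recorded only while the device is worn. A patient who sits no more than before but wears the device for longer records more sedentary time. As defined, the outcome cannot separate the two.

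If wear differs little between arms, or varies to the same extent in both, the result is extra noise in a secondary outcome. If mean wear changes differently between arms after baseline, the time-by-arm term picks it up as a treatment effect. The direction is awkward: if the intervention arm came to wear the device for longer, it would appear to sit more, which could mask or reverse a true reduction. MVPA minutes are open to the same mechanism, but they are a small part of the worn day.

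**Working it through.** **Inputs from the protocol article.** Requested wear 12 h; minimum valid wear 8 h; mean MVPA 38 min, SD 18.1; target difference 20%; 80% power; 5% significance; intra-cluster correlation 0.05; cluster size 8; dropout 15%; 279 patients.

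**Assumptions, not in the documents.** Sedentary share of worn time 50-80%. The 38 min accrue evenly over a worn day of 8 to 12 h. Any between-arm gap in wear is hypothetical.

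**1. The plan's own figures.**
- Target: 0.20 × 38 = 7.6 min.
- Patients per arm: 2 × [18.1 × (1.960 + 0.842) / 7.6]² = 89.0, as stated.
- Design effect: 1 + (8 − 1) × 0.05 = 1.35. Then 2 × 89 × 1.35 = 240.3 patients, and 240.3 / 8 = 30.04 practices, as stated.
- Dropout: 240.3 / 0.85 = 283, against the stated 279 = 31 × 9.

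The 7.6-min yardstick is therefore sound.

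**2. Ceiling on sedentary minutes.** 8 × 60 = 480 and 12 × 60 = 720. Wear alone moves the ceiling by 240 min. This step needs no assumption.

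**3. What biases the comparison.** With a time-by-arm term, a stable difference in wear between arms cancels. The bias is

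rate per worn hour × (change in mean wear, intervention − change in mean wear, control).

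Equal changes give zero bias.

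**4. Sedentary outcome.** The rate is share × 60: 0.5 × 60 = 30 to 0.8 × 60 = 48 min per hour. A differential change of 30 min adds 15-24 min of apparent sitting.

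**5. MVPA.** The rate is 38/12 = 3.17 to 38/8 = 4.75 min per hour.

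| Differential change in mean wear | Shift in MVPA | Share of 7.6 min |
|---|---|---|
| 15 min | 0.8-1.2 min | 10-16% |
| 30 min | 1.6-2.4 min | 21-31% |
| 60 min | 3.2-4.8 min | 42-63% |

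To equal the whole target, the differential change would have to be 7.6/4.75 = 1.6 h to 7.6/3.17 = 2.4 h. On a 12 h day the sedentary shift is 30/3.17 to 48/3.17, about 9 to 15 times the MVPA shift.

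**6. Does the proposed scale help?** Suppose 30 min are added to a 12 h day. If they have the same mix as the rest of the day, the sedentary percentage does not move. In the worst case they are wholly sedentary. Raw minutes then rise by 30, and minutes per 12 h worn rise by 30 × (1 − share) × 720/750: 14.4 min at a 50% share and 5.8 min at 80%. The distortion is at least halved, though not always removed.

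**The case against.** A reader might infer that wear differences between arms do contaminate the primary outcome. The documents do not support that.
- No wear gap is reported or predicted. Both arms have the same instruction and the same validity rule.
- The research team, not the unblinded nurses, distributes the devices at T1 and T2 (Data collection). Patients are kept unaware of randomisation and allocation.
- The text on the intervention asks for accelerometer self-monitoring for two weeks after the first consultation. Table 1 marks the technique for all four consultations, but the last is at week 12 and the primary endpoint is at 6 months. Nothing shows that a wear habit lasts until then.
- The 38 min come from another trial, and no wear time is given for it. If the added hours are inactive, the MVPA shift is smaller than shown.

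One patient at 8 h against 12 h would show 38 × 8/12 = 25.3 against 38 min, a gap larger than the target. That compares two wear times in one person and says nothing about a difference between arms.

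It would also go too far to say that wear dominates the sedentary result or reverses its sign. Both depend on a gap, a sedentary share and an effect size that the documents do not give.

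Finally, a statistical analysis plan that is not shown may add a wear-time covariate, and the provision for sensitivity analyses on outcome definitions leaves room for one. That stands for the model. It does not fully answer the point on sedentary behaviour, because the article itself fixes that outcome as raw minutes.

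**Conclusion.** The point holds for sedentary behaviour: its stated scale mixes sitting with wear, at 30-48 min per extra worn hour if 50-80% of worn time is sedentary. Whether this produces bias or only noise depends on whether wear changes differently between arms. That is possible, because one arm uses an accelerometer as part of treatment, but it is not shown.

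For MVPA the same risk is smaller and equally conditional: about 1.6-2.4 min for a 30-min differential change, assuming proportional accrual over 8-12 h. This does not justify replacing the primary analysis. The sample size is unaffected.

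**What to change.** - Define sedentary behaviour as the percentage of wear time below 1.8 METs, or as minutes per 12 h worn.
- Report mean daily wear time by arm at T0, T1 and T2, so that a reader can see whether a gap arose.
- Keep unadjusted MVPA minutes as the primary analysis. Name one sensitivity analysis that adds each visit's mean daily wear hours to the model.

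The order of the two MVPA results matters. Wear time is measured after allocation, and if the intervention leads patients to wear the device for more of an active day, adjusting for it could remove part of a real effect.

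The cost is a few sentences. The 8 h rule cannot be applied without wear time, so the variable must already be available. Patient procedures do not change. The article describes the trial as still collecting data, so at that stage the rule could be fixed before the analysis.

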#### Secondary outcomes

The following are secondary outcomes of this trial:Sedentary behaviour using the accelerometer to measure the number of minutes in the sedentary category (<1.8 METs)Self-efficacy for physical activity using the Exercise Self-efficacy Scale [47–49]Patient activation using the PAM-13 short form [50, 51]Health status using the EQ-5D questionnaire [52]

Potential effect modifiers to investigate which patient characteristics modify change in physical activity level include age, depression measured using the Hospital Anxiety and Depression Scale [53, 54], body mass index (BMI), level of education, social support using the Multidimensional Scale of Perceived Social Support [55], patient-provider relationship using the Communication Assessment Tool [56], and baseline number of minutes of moderate to vigorous level of physical activity using the accelerometer.

#### Process evaluation

A mixed method process evaluation will be performed at the end of the study. To evaluate treatment fidelity [34, 57, 43], nurses allocated to the study arm will randomly audiotape one consultation from among the four consultations. The audiotapes will be coded using a coding list developed specifically for this study, consisting of the content of each of the four consultations and the Behaviour Change Counselling Index [58]. Additionally, nurses will be instructed to self-report the presence of the patient and the discussed content during a consultation, the time needed per consultation, and reasons for the patient’s dropout if applicable. To evaluate the nurses’ perceptions of their capability, motivation, self-efficacy and outcome expectancy of applying the BCTs integrated into the Activate intervention, nurses will be asked to complete the self-assessment at the start of the training, after the training, during the intervention period, and at the end of the study. At the end of the study, nurses in the intervention arm will be invited to a semi-structured interview to explore their experiences in delivering the intervention. Included topics are perceptions of the study procedures, barriers to and facilitators of implementation of the intervention, applying the BCTs, the training programme, self-efficacy, motivation of nurses and patients, perceived effect of the intervention, and their evaluation of the acceptability of the intervention for implementation in routine primary care. Furthermore, descriptive data will be collected to identify existing socio-demographic variation in who received the intervention and who dropped out of the intervention.

To explore patients’ experiences with the intervention, patients in the intervention group will be asked additional questions in the T1 questionnaire. To deepen our understanding of patients’ experiences, a sample of patients from the intervention group will be invited to a semi-structured interview at the end of the study. Included topics in the T1 questionnaires and interviews are perceptions of the outcome, capability, self-efficacy, motivation, intention, opportunity, barriers and facilitators, and satisfaction with the intervention.

